### Who will be included in each analysis {27b}

All randomized participants will be included in each analysis as randomized.

### How missing data will be handled in the analysis {27c}

If a participant is required to receive the other group’s treatment or switch to the control group (e.g., if they experience significant pain during exercise), or if values are missing for any reason (e.g., dropout or loss to follow-up), this is accounted for using ITT analysis. This means that participants are analyzed in the group to which they were randomized, and missing values are imputed. The imputation method (single or multiple imputation) is determined according to the guidelines of Jakobsen et al. [42] at the end of data collection.

### Methods for additional analyses (e.g., subgroup analyses) {27d}

No additional analyses (e.g., subgroup and adjusted analyses) are planned.

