### Sample size {19}

An a priori sample size estimation based on the results of pilot measurements [40] examining change in dynamic balance after 6 weeks of balance training using the Mini Stability Trainer indicated that 33 participants (11 per group) would be needed to detect a mean difference of 4.6% in the composite score of the YBT with an effect size of *f* = 0.33 and a probability of 1 − *β* = 0.9 at a significance level of *α* = 0.05. To account for potential dropouts and loss to follow-up, the target number of participants is 36 (12 per group).

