## Statistical methods

### Statistical methods for primary and secondary outcomes {27a}

Primary and secondary outcome measures are reported descriptively using mean ± SD or median and interquartile range according to their type (e.g., ordinal or interval scale). After testing the data for normal distribution using the Shapiro-Wilk test and histograms, for the primary outcomes of dynamic balance (YBT) and postural stability (MBESS), the significance of differences in post-intervention change within and between groups will likely be analyzed using repeated measures analysis of variance (ANOVA) (YBT) or Friedman tests or Kruskal-Wallis tests (MBESS) and post hoc tests with Bonferroni correction to account for multiple testing. After testing the data for normal distribution using the Shapiro-Wilk test and histograms, for the secondary outcome of gait biomechanics, the significance of differences in post-intervention change within and between groups will likely be analyzed using repeated measures analysis of variance (ANOVA) and post hoc tests with Bonferroni correction to account for multiple testing. For the secondary outcome of joint function (FAAM), the significance of differences in post-intervention change within and between groups will be analyzed using Friedman tests or Kruskal-Wallis tests and post hoc tests with Bonferroni correction to account for multiple testing. The global significance level is set to *α* = 0.05. No additional analyses are planned.

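### The between-group YBT comparison is planned as an analysis of raw change with no baseline covariate; ANCOVA on the baseline already collected would be somewhat more precise

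*Protocol article*

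**What the plan says.** Item 27a (statistical methods) says that the primary YBT outcome "will likely be analyzed using repeated measures analysis of variance (ANOVA) (YBT"), following a step worded as "After testing the data for normal distribution using the Shapiro-Wilk test and histograms". The tests concern post-intervention change within and between groups, with Bonferroni-corrected post hoc tests. The same approach is named for gait biomechanics.

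Item 16 (outcomes) defines the YBT and gait comparisons as the difference in change between groups, calls the analysis parametric, and gives two measurement times: before and after the 6 weeks. Item 18 (participant timeline) has outcome measures completed first and the group envelope opened afterwards.

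Item 27a plans no additional analyses. Item 27d spells this out: "No additional analyses (e.g., subgroup and adjusted analyses) are planned".

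Item 19 reports a calculation from pilot data that calls for 33 people, 11 in each arm, to show a 4.6% mean difference in the YBT composite. Its inputs are f = 0.33, power 0.90 and α = 0.05. Allowing for dropout, "the target number of participants is 36 (12 per group"). No standard deviation and no correlation between baseline and post values is stated.

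**The concern.** A change analysis subtracts the whole baseline value, which fixes the baseline slope at 1. ANCOVA estimates that slope. When the correlation is below 1, the change score over-corrects and carries extra noise into the group difference. With small arms this is worth attention: the chance difference in mean baseline between two arms of 12 has a standard deviation of √(2/12) = 0.41 baseline SDs.

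Item 27a also leaves the final test open. The wording is conditional and the choice follows a look at the distribution of the outcome data, so the model for a primary outcome is not fully fixed beforehand.

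At stake is precision that the trial could have from data it already collects. The type I error of the planned test is not in question.

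**Working it through.** **Inputs.** From item 19: f = 0.33, α = 0.05, power 0.90, three groups, N = 33 (target 36). From item 16: m = 2 measurement times. The correlation ρ between baseline and 6-week values is not in the article; it is an assumption here, shown over a range.

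**Step 1. Reproduce the planned sample size.** For the group-by-time interaction, λ = f²·N·m/(1 − ρ), with 2 and N − 3 degrees of freedom. With ρ = 0.5:

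λ = 0.33² × 33 × 2 / 0.5 = 14.37; F with 2 and 30 df; power 0.907.

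At N = 32 the power is 0.897, so 33 is the smallest N that reaches 0.90. The planned figure is reproduced exactly with ρ = 0.5. Other correlations do not match (ρ = 0.3 gives 44, ρ = 0.7 gives 21), nor does a one-way ANOVA at f = 0.33 (120). At the target of 36, λ = 15.68 and power is 0.933.

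**Step 2. Compare the variances in large samples.** Let s be the SD at each time, taken as equal at baseline and 6 weeks.

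- Change score: 2s²(1 − ρ)
- ANCOVA: s²(1 − ρ²)
- Ratio ANCOVA/change: (1 + ρ)/2

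**Step 3. Allow for estimating the slope.** Chance baseline imbalance together with an estimated slope inflates the variance of an adjusted pairwise difference, on average, by 1 + 1/(N − k − 2), where k = 3 is the number of groups. With N = 36 this is 1 + 1/31 = 1.032. A simulation at 12 per arm agrees with the net column to within about 0.2 percentage points.

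| Assumed ρ | Ratio (1 + ρ)/2 | Large-sample reduction | Net reduction, 12 per arm |
|---|---|---|---|
| 0.5 | 0.75 | 25% | 1 − 0.75 × 1.032 = 22.6% |
| 0.7 | 0.85 | 15% | 12.3% |
| 0.8 | 0.90 | 10% | 7.1% |
| 0.9 | 0.95 | 5% | 1.9% |
| 0.95 | 0.975 | 2.5% | −0.6% |

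**Step 4. Translate to power under the plan's own inputs (ρ = 0.5).** At N = 36, λ rises from 15.68 to 15.68/0.75 = 20.91 with 2 and 32 df. Power goes from 0.933 to 0.980, or 0.977 after the 1.032 inflation. Put the other way, 90% power would need 27 participants (9 per group) instead of 33.

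**Step 5. Gait.** Item 16 cites mean intraclass correlations of 0.95 to 0.97 for instrumented gait analysis. If the 6-week correlation were that high, the last row of the table would apply and ANCOVA would gain nothing. The correlation over 6 weeks is probably lower than a reliability coefficient, so this marks one end of the range and is not an estimate.

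**The case against.** The strongest reply is that this is a preference about efficiency. Under randomisation, an analysis of change is unbiased and holds its level, and Step 1 shows adequate power for the planned test under the plan's own inputs. That stands. A reader might infer that the missing covariate makes the YBT analysis invalid or leaves the trial underpowered. The article supports neither: lower power figures for the planned test can be produced only by choosing an SD of change that the article does not give.

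It can also be said that repeated measures ANOVA does use the baseline. That is correct: baseline enters as the first repeated measure. What is absent is baseline as a covariate with its own slope.

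Item 27d sits under additional analyses, and covariates are often left to an analysis plan. This weakens item 27d as evidence on its own. But item 27a names the primary model without a covariate and also says nothing further is planned, so the article does fix the choice.

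On the normality test, a reader might infer that the YBT analysis is wholly data-driven. Item 16 already commits YBT and gait to parametric analysis, and histograms are used alongside the Shapiro-Wilk test. What remains is conditional wording that is easily removed.

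Bonferroni is valid for the three pairwise comparisons. A closed procedure would be an option with three groups, but it is a separate preference and not a correction.

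Finally, ANCOVA answers only the between-group question. Item 10 also asks whether each training group improves, so replacing the whole YBT analysis would drop a stated objective.

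**Conclusion.** The point holds as a moderate, inexpensive improvement to the between-group YBT analysis. At 12 per arm, ANCOVA would reduce the variance of a group difference by about 22 to 23% if ρ is 0.5, 12% if 0.7, 7% if 0.8 and 2% if 0.9. The value 0.5 is the one that reproduces the planned 33, but it is inferred from that match and is not stated. The figures assume equal variances at the two times and a linear relation with a common slope. The gain is not entirely free: it uses one error degree of freedom, and estimating the slope takes about 2 to 3 percentage points off the large-sample figure.

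It would be tempting to carry the same gain over to gait. The only relevant figures in the article, the intraclass correlations of 0.95 to 0.97, do not support that.

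**What to change.** In item 27a:

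- Name ANCOVA of the 6-week YBT composite on group and baseline composite as the between-group analysis, reporting adjusted pairwise differences with 95% confidence intervals.
- Delete *likely* and state that the model does not depend on the Shapiro-Wilk result; check the residuals as a diagnostic.
- Keep the within-group analysis of change for the item 10 objective, and keep Bonferroni if preferred.

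Amend item 27d so that it no longer excludes baseline adjustment. The same model may be used for gait parameters, without a claim of a precision gain.

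The cost is a change of wording, notified to the ethics committee and the registry as item 31 requires. No new data are needed. The change should be made before the outcome data are analysed.

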### Interim analyses {28b}

No interim analyses are planned.

### Protocol and statistical analysis plan {5}

DRKS (German Clinical Trials Register)—DRKS00034295, https://drks.de/register/de/trial/DRKS00034295/preview

## Oversight and monitoring

### Composition of the coordinating center and trial steering committee {3d}

Data will be monitored by the assessor (AB) immediately after recording and documentation. All data will be monitored and analyzed by the blinded principal investigator (MA). Participants will be seen regularly during the intervention to adjust the exercise protocol if necessary. As there is no risk of harm to participants, a formal data monitoring committee is not required for this study.

### Frequency and plans for auditing trial conduct {29}

Not applicable.

### Protocol amendments {31}

Any changes to the trial protocol will be communicated to the ethics committee and the trial registry.

### Dissemination policy {8}

We will share our research with academic and professional audiences by presenting at conferences and publishing our findings in high-impact journals.

## Discussion

The purpose of this study is to evaluate the effects of targeted forefoot and rearfoot stability training on the primary measures of dynamic stability and postural stability, as well as the secondary measures of gait biomechanics and self-reported function on the CAI. We hypothesize that the targeted forefoot and rearfoot group, as well as the wobble board group, will show significant improvements in the aforementioned measures but will not show significant differences between these intervention groups. Since there is currently a lack of information regarding targeted forefoot and rearfoot exercises on ankle stability, this study has the potential to improve long-term outcomes regarding CAI and provide an alternative to healthcare practitioners in treatment. The data from this study could therefore be used in the future to develop treatment plans for CAI.

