### Objectives {10}

The study will be guided by the following specific objective: To determine whether the outcomes of dynamic balance, postural stability, gait biomechanics, and joint function improve in the intervention group and the balance training group after a 6-week intervention period and whether there is a significant difference compared to the control group.

The study is also based on the following hypotheses:The intervention group and the balance training group will lead to similar significant improvements in outcomes compared to the control group.It is also hypothesized that there will be no significant differences between the intervention group and the balance training group.

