### Trial design {12}

This study protocol follows the “Standard Protocol Items: Recommendations for Interventional Trials (SPIRIT) 2013 Statement” (https://www.equator-network.org/reporting-guidelines/spirit-2013-statement-defining-standard-protocol-items-for-clinical-trials/). The study is a prospective, single-center, interventional, randomized controlled trial with an intervention group (forefoot and rearfoot stability training) and two comparison groups, either a usual balance training group or a control group. It is a single-blind (principal investigator) design with patients randomized 1:1:1 to one of the three parallel groups. To ensure internal validity, a control group is included that does not receive any balance training intervention. Because many patients with CAI do not seek medical or physical therapy and continue with their usual activities, participants in the control group are allowed to do so. A summary of study information is presented in Table 1.

**Table 1 Tab1:** Study information

Category	Information
Country	Germany
Intervention	Active part: 6 weeks of training with the Mini Stability Trainer according to a predefined exercise schedule; 6 weeks of training with the Wobble Smart Board according to a predefined exercise schedule; one training session is performed under the supervision of a member of the study team, at least 17 training sessions are performed independently by each subject at home Control group: activities of daily living and sports activities; balance exercises are not allowed
Inclusion and exclusion criteria	Inclusion criteria: age between 18 and 44 years; based on the guidelines of the International Ankle Consortium: history of at least one ankle injury more than 1 year ago with typical signs of inflammation; self-reported ankle instability; in addition, two or more episodes of “giving way” must have occurred within the previous 6 months; Cumberland Ankle Instability Tool (CAIT ^a^) score ≤ 24 (in the case of bilateral ankle instability, the more severely affected side is selected) Exclusion criteria: acute injury, surgery or fracture of the lower extremity, neurological disorders, chronic overuse injuries such as Achilles or patellar tendinopathy; current participation in a targeted ankle rehabilitation program

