### Outcomes {16}

#### Primary outcome measurements

##### Y-Balance Test

The Y-Balance Test (YBT) is a test of dynamic balance and is administered using a standardized test kit [25, 26]. In this study, the participant stands barefoot with the test leg on the stance platform of the test kit with the most distal portion of the big toe at the starting line. The hands are placed on the left and right iliac crest. The participant is instructed to move the target (reach indicator) with the free leg along the pipe as far as possible in the anterior, posteromedial, and posterolateral directions and to hold the end position for 3 s. Six trials are performed in each direction [27]. The first 3 trials are used to familiarize the participant with the task. The following 3 trials are recorded from the tape measure (5 mm increments) of each pipe at the edge of the reach indicator, at the point where the most distal point of the foot reaches, and used for further analysis. The participant is instructed to maintain balance during the trials and to return to the starting position after each trial. A trial is considered invalid and will be repeated if the participant touches the ground with the free leg, slips with the standing foot, falls off the stance platform, loses contact with the reach indicator while moving it to the maximum reach position, kicks the reach indicator forward, places the foot on the top of the reach indicator, or fails to return to the starting position under control. The maximum number of attempts is 3. The left leg is measured first. In addition, leg length is measured from the anterior superior iliac spine to the medial malleolus with the participant in the supine position to normalize anterior, posteromedial, and posterolateral reach distances to leg length. The following formula is used for normalization: reach distance/leg length × 100. The means of these normalized values are then calculated. In addition, the composite score is calculated using the following formula: (sum of the 3 reach distances)/3 times leg length × 100. In this study, the results are presented using the composite score. The minimum detectable change in YBT is between 7.7 and 14% [28]. The difference in change between the groups is assessed and calculated using parametric statistical analysis. The aggregation method is mean ± SD, and the measurements are taken before and after the 6-week intervention.

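### The plan mostly judges training against control, but three places leave a within-arm route to the same claim, which a retest gain shared by all arms could satisfy

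*Protocol article*

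**What the plan says.** The protocol states the control comparison in several places.

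- Objectives {10}, first hypothesis: "The intervention group and the balance training group will lead to similar significant improvements in outcomes compared to the control group".
- Y-Balance Test (YBT): "The difference in change between the groups is assessed and calculated using parametric statistical analysis". The sections on the Modified Balance Error Scoring System (MBESS), the Foot and Ankle Ability Measure (FAAM) and gait define their contrasts in the same way.
- Table 1 (study type) and Explanation for the choice of comparator {9b} also set training against the control group.
- Trial design {12} gives the reason for that arm: "To ensure internal validity, a control group is included that does not receive any balance training intervention".

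Three places leave room for a different criterion.

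- The objective in {10} has two clauses. The first asks whether outcomes "improve in the intervention group and the balance training group after a 6-week intervention period". Only the second asks "whether there is a significant difference compared to the control group".
- Statistical methods {27a} says that "the significance of differences in post-intervention change within and between groups will likely be analyzed using repeated measures analysis of variance (ANOVA) (YBT". For the MBESS it lists "Friedman tests or Kruskal-Wallis tests (MBESS) and post hoc tests with Bonferroni correction", and it gives the same choice for the FAAM. It does not say which of the within-group and between-group results decides.
- The Discussion gives the hypothesis as both training groups "will show significant improvements in the aforementioned measures but will not show significant differences between these intervention groups". Control does not appear in that sentence.

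**The concern.** A pre-post test inside one arm asks whether the mean 6-week change is zero. It does not ask whether training adds anything to the change that occurs without training. Any gain common to all arms, such as learning the test or trying harder the second time, makes the within-arm test reject even when training does nothing. The YBT uses three familiarisation trials per direction, so it is a task on which people can improve by practice. A Friedman test compares time points within participants and makes no comparison with control.

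At stake is which sentence a result would confirm. Suppose both training arms change significantly, and neither differs significantly from control or from the other. The Discussion sentence would be met and the hypothesis in {10} would not. The protocol provides significance tests for both readings and does not rank them.

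**Working it through.** **1. The plan's own sample size.** Sample size {19} gives f = 0.33, α = 0.05, power 0.90 and 33 participants. Take a repeated-measures ANOVA with 3 groups and 2 time points, and assume a pre-post correlation ρ = 0.5 (not stated in the document). The group-by-time noncentrality is λ = f²·N·m/(1 − ρ) = 0.1089 × 33 × 2/0.5 = 14.37, with 2 and 30 degrees of freedom.

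- N = 33: power 0.9075. N = 30: power 0.874. So 33 is the smallest multiple of 3 that reaches 0.90, and the stated figure reproduces.
- N = 36: power 0.933.
- The within-subject time effect at the same ρ needs only 27. At ρ = 0.4 it also gives 33, so the match supports a between-group contrast of change but does not prove it.

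**2. Null trials with a shared retest gain.** Inputs: n = 12 per arm (from {19}), normally distributed change, no training effect, and the same gain g in all three arms, in SDs of change. The range of g is an assumption. The documents give neither a retest gain nor an SD of change, so g is not converted to YBT points.

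Within one arm, t = mean change/(SD/√12), with 11 degrees of freedom and noncentrality g√12. A result counts only if it is an improvement. The arms are independent, so the probability for both is the square.

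Example, g = 0.5: noncentrality 0.5 × 3.464 = 1.732.
- At two-sided 0.05 (critical t 2.201): one arm 0.353, both arms 0.353² = 0.124.
- At 0.05/3 (critical t 2.820): one arm 0.189, both arms 0.036.

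| Gain (SD) | One arm, 0.05 | Both arms, 0.05 | One arm, 0.05/3 | Both arms, 0.05/3 |
|---|---|---|---|---|
| 0.3 | 16% | 2.4% | 7% | 0.5% |
| 0.5 | 35% | 12% | 19% | 3.6% |
| 0.66 | 55% | 30% | 34% | 12% |
| 0.8 | 71% | 51% | 51% | 26% |
| 1.0 | 88% | 78% | 73% | 53% |

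Also requiring that the two training arms do not differ (two-sample t test on change at 0.05/3, by simulation) barely alters the figures for both arms: at 1.0 SD the uncorrected 78% becomes 77%, and the 53% stays at 53%.

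**3. The contrast that includes control.** In the same simulated trials, the three-arm test on change (the group-by-time comparison) rejects in about 5% at every gain, because a gain common to all arms cancels. If within-arm tests at 0.05/3 were read only after that test is significant, the Discussion pattern occurs in about 1% of trials or less up to 0.8 SD, and in 1.6% at 1.0 SD.

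**The case against.** The strongest reply is that the control contrast is already the plan. The hypothesis in {10}, Table 1, {9b} and all four outcome definitions state it, {27a} includes between-group tests, and the sample size reproduces as a group-by-time interaction. The Discussion sentence is a recap that names no test, level or decision rule. The Bonferroni correction in {27a} may cover the within-arm tests, which lowers the figures, and post hoc tests are often read only after a significant overall test. The familiarisation trials are there to reduce learning. Within-arm results beside between-arm results are common secondary reporting.

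Most of this stands. A reader might infer that efficacy is tested only within arms, or that the Discussion sets a rule that overrides the statistical section. The documents support neither reading. Nor do they show that a shared gain would pass the planned between-group test more often than the nominal 5%.

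The reply does not remove the inconsistency. The article states the hypothesis once with control and once without, makes improvement in the training arms a question of its own, and plans significance tests that answer it. It does not say that post hoc tests wait for a significant overall test, and the Friedman option offers a significance test with no control comparison. These are statements in the text, so this is more than detail left to an analysis plan.

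**Conclusion.** The point holds in a limited form. The plan mostly asks the right question, but the objective's first clause, the within-group tests in {27a} and the Discussion sentence leave a route by which change within the training arms alone could be read as efficacy.

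If that route carried the claim, the chance of a false conclusion that both arms benefit, with no difference between them, would run from about 2% to 78% uncorrected, or about 0.5% to 53% at 0.05/3, for assumed shared gains of 0.3 to 1.0 SD. The group-by-time test stays at about 5%. These figures rest on 12 completers per arm, normal change, an equal gain in all arms and gain sizes that the documents do not supply. They show how exposed the within-arm reading is. They are not the error rate of the plan as a whole.

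The contrast with control removes only a gain that the arms share. Who will be blinded {24a} says that the observer is not blinded at the post-measurement, and any bias from this that differs between arms would remain.

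**What to change.** Align three places before the analysis.

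- **Objectives {10}:** make the objective one question. Improvement due to training is the 6-week change in a training arm minus the 6-week change in the control arm.
- **Statistical methods {27a}:** state that the group-by-time comparison decides, followed by two pre-specified contrasts, Mini Stability Trainer against control and Wobble Smart Board against control. For the MBESS and FAAM, let the between-group comparison of change decide, not a Friedman test. Report each arm's change descriptively with a 95% CI, and state that no within-arm p-value supports an efficacy claim.
- **Discussion:** reword the hypothesis so that both training groups are expected to show greater improvement than the control group.

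This needs no new data, visits or participants, and the sample size stays as it is. Under Protocol amendments {31} the change would go to the ethics committee and the registry. The downside is that the sponsor can no longer claim efficacy from significant pre-post change within an arm.
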